# Steps to recovery: body weight-supported treadmill training for critically ill patients: a randomized controlled trial

**DOI:** 10.1186/s13063-020-04333-y

**Published:** 2020-05-15

**Keywords:** ICU, intensive care, rehabilitation, physical function, body weight-supported treadmill, critically ill, ambulation, intervention

## Abstract

**Background:**

Early mobilization has been proven effective for patients in intensive care units (ICUs) to improve functional recovery. However, early mobilization of critically ill, often mechanically ventilated, patients is cumbersome because of the attachment to tubes, drains, monitoring devices and muscle weakness. A mobile treadmill with bodyweight support may help to initiate mobilization earlier and more effectively. The aim of this study is to assess the effectiveness of weight-supported treadmill training in critically ill patients during and after ICU stay on time to independent functional ambulation*.*

**Methods:**

In this randomized controlled trial, a custom-built bedside body weight-supported treadmill will be used and evaluated. Patients are included if they have been mechanically ventilated for at least 48 hours, are able to follow instructions, have quadriceps muscle strength of Medical Research Council sum-score 2 (MRC 2) or higher, can sit unsupported and meet the safety criteria for physical exercise. Exclusion criteria are language barriers, no prior walking ability, contraindications for physiotherapy or a neurological condition as reason for ICU admission. We aim to include 88 patients and randomize them into either the intervention or the control group. The intervention group will receive usual care plus bodyweight-supported treadmill training (BWSTT) daily. The BWSSTT consists of walking on a mobile treadmill while supported by a harness. The control group will receive usual care physiotherapy treatment daily consisting of progressive activities such as bed-cycling and active functional training exercises. In both groups, we will aim for a total of 40 minutes of physiotherapy treatment time every day in one or two sessions, as tolerated by the patient. The primary outcome is time to functional ambulation as measured in days, secondary outcomes include walking distance, muscle strength, status of functional mobility and symptoms of post-traumatic stress. All measurements will be done by assessors who are blinded to the intervention on the regular wards until hospital discharge.

**Discussion:**

This will be the first study comparing the effects of BWSTT and conventional physiotherapy for critically ill patients during and after ICU stay. The results of this study contribute to a better understanding of the effectiveness of early physiotherapy interventions for critically ill patients.

**Trial registration:**

Dutch Trial Register (NTR) ID: NL6766. Registered at 1 December 2017.

## Introduction and rationale

There is an increasing amount of evidence stating that early mobilization and activation of patients admitted to the intensive care unit (ICU) improves functional recovery [1–7]. Current practice may include active sitting and standing up exercises, cycling on a cycle ergometer with upper or lower limbs (while in bed or in a chair) and ambulation training whenever possible. However, practicing walking with critically ill patients after a longer period of mechanical ventilation on the ICU is demanding because of muscle weakness and the attachment of patients to mechanical ventilation, drains, infusion lines and monitoring equipment [8]. Moreover, ambulating critically ill patients puts a large demand on staff as it often requires at least three persons and a considerable amount of time [9]. Innovation and new technological developments may facilitate ambulation training in patients experiencing these difficulties and may also improve the feasibility, safety and effectiveness of early mobilization in the intensive care unit [10, 11].

Body weight-supported treadmill training (BWSTT) has shown to be an effective modality for improving fitness, walking capacity and daily functioning in different rehabilitation populations with muscle weakness [12–14]. In a previous pilot study, we showed that BWSTT was feasible and safe in critically ill patients [12]. Early ambulation training on the ICU supported by BWSTT can potentially shorten the time to independent ambulation for critically ill patients and improve their functional status at ICU and hospital discharge.

The aim of this study is to assess the effect of BWSTT in critically ill patients during ICU and hospital stay on time to independent functional ambulation as compared to usual care.

We hypothesize that BWSTT leads to earlier independent functional ambulation compared to usual care.

## Methods

### Study design

A monocenter randomized controlled trial (RCT) will be executed on the ICU and general wards of the Amsterdam University Medical Center, location AMC (Amsterdam UMC) between May 2018 and September 2020. The Amsterdam UMC houses a mixed medical and (neuro) surgical ICU with 26 beds.

### Eligibility criteria

As we aim to include patients who are at risk for prolonged rehabilitation, we focus on patients with a longer duration of mechanical ventilation [15–17].

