#### Inclusion criteria

Participants have to be mechanical ventilated for ≥ 48 hours, must be responsive and able to follow instructions according to the Short 5-item Questionnaire (S5Q 5 out of 5) [18], have quadriceps muscle strength ≥ 2 according to the Medical Research Council [19] and must be able to sit unsupported on the edge of the bed.

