### Randomization and blinding

We will use a variable block randomization method performed by the software CASTOR EDC, a Good Clinical Practice (GCP)-approved online software service. These variable blocks are of various sizes. This way the researcher does not know how large the blocks are at any given moment, and thus cannot predict the next randomization. After randomization, the patient identification number (PIN) number and treatment allocation will be provided to the physiotherapist performing the interventions. Due to the kind of the intervention, it is not possible to blind physiotherapists and participants for the intervention. The primary outcome will be assessed by a researcher who is blinded for the intervention. Secondary outcomes will be assessed by blinded researchers except during the stay of the participants in the ICU where measurements will be assessed by the physiotherapist during treatment (usual care and intervention) to avoid too much strain on the patients.

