#### Secondary endpoints

The secondary endpoints are walking distance as measured with the 2 Minutes Walking Test (2MWT) [22], muscle strength of upper and lower extremities as measured with the Medical Research Council sum-score (MRC sum-score) [19], perceived exertion after physiotherapy interventions as measured with the Rating of Perceived Exertion scale (RPE scale) [23], physical strain during physiotherapy interventions as measured by peak values of heart rate, mean arterial pressure, respiratory frequency and oxygen saturation, functional mobility as measured with the De Morton Mobility Index (DEMMI) [24, 25], duration of mechanical ventilation, ICU, and hospital length of stay, discharge destination, symptoms of post-traumatic stress as measured with the Posttraumatic Stress Disorder Checklist (PCL-5) [26] and patient satisfaction as measured with a 5-point Likert scale. (Serious) Adverse Events (S) AEs related to the study intervention will be recorded in accordance with good clinical practice guidelines and legislation. Physiotherapy intervention characteristics including numbers of staff and time needed, frequency and content of treatment and walking time, distance and support needed during BWSTT will be recorded for both groups. Outcomes will be assessed at different points in time as is shown in Fig. 2.

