#### Statistical analysis

Sample size was calculated using data from previous studies where BWSTT [12] and usual care [24] was provided to critically ill patients in the Amsterdam UMC. Data of 35 patients were retrieved. On average, these patients reached the endpoint (≥ FAC 3) at day 15 after the inclusion criteria were met. In the sample data, we found a hazard ratio of 1.87 at 15 days in favor of BWSTT. All patients reached the endpoint within the study period. Given a type 1 error rate of 5% and a power of 0.8 the analysis resulted in a required sample size of 88 (44 + 44) patients before correction for attrition, assuming a 10% dropout rate. A check on sample size assumptions will be performed after inclusion of 40 participants as the dataset used for sample size to calculate was relatively small.

The primary objective of this study is to assess the effect of BWSTT in critically ill patients on time to functional ambulation as compared to usual care. For this, Kaplan-Meier analyses will be performed and comparisons between both groups will be made. For the primary analysis we will use intention to treat principles. Multiple imputation will be applied in cases where the primary outcome is missing. Cox regression analysis will be performed when imbalances between groups are found at baseline in age (mean difference ≥ 10%), muscle strength (MRC sum-score mean difference ≥ 10%), functional ambulation level (FAC mean difference > 1) and co-morbidities (Charlson Comorbidity Index [CCI] mean difference > 1) as they are potentially related to the primary outcome. Significance values are not considered when determining baseline differences.

The secondary objective of this study is to analyze between group differences of other patient relevant outcome measures for the evaluation of BWSTT. Patient characteristics and secondary study endpoints will be described using descriptive statistics according to their distribution. If the variables are normally distributed, they are expressed as mean and standard deviation (SD). Skewed variables are presented with medians and interquartile ranges (IQR). Between groups comparisons will be made using the appropriate tests according the variable type and distribution.

For this study, analysis will be performed using the software package R version 3.6.1.

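### Ventilation duration, the protocol's own marker of slow recovery, is missing from the covariates named for the primary outcome, which leaves chance imbalance uncorrected and some precision unused

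*Protocol article*

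**What the plan says.** All references are to the protocol article.

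- **Eligibility criteria** gives the reason for selecting on ventilation: "As we aim to include patients who are at risk for prolonged rehabilitation, we focus on patients with a longer duration of mechanical ventilation".
- **Inclusion criteria** sets a lower bound only: "Participants have to be mechanical ventilated for ≥ 48 hours".
- **Randomization and blinding**: "We will use a variable block randomization method performed by the software CASTOR EDC". No stratification factor is stated.
- **Statistical analysis** makes the primary comparison as follows: "Kaplan-Meier analyses will be performed and comparisons between both groups will be made". A Cox model is conditional: "Cox regression analysis will be performed when imbalances between groups are found at baseline in age (mean difference ≥ 10" per cent), with further triggers for "muscle strength (MRC sum-score mean difference ≥ 10%), functional ambulation level (FAC mean difference > 1") and for "co-morbidities (Charlson Comorbidity Index [CCI] mean difference > 1) as they are potentially related to the primary outcome". Ventilation duration is not among the four.
- **Secondary endpoints** is the only place where the duration appears as a variable: "duration of mechanical ventilation, ICU, and hospital length of stay". The patient characteristics listed after Fig. 2 do not name the duration before randomisation.

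**The concern.** The four covariates are named because they may relate to time to FAC 3. By the protocol's own argument under Eligibility criteria, ventilation duration passes the same test: it is offered as the marker of prolonged rehabilitation, which is close to what the primary endpoint measures. The entry criteria restrict current function (command following, quadriceps strength, unsupported sitting) but put no ceiling on ventilation history. Two patients with similar MRC and FAC scores at entry may have been ventilated for very different times.

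Two things are at stake. If one arm happens to receive the longer-ventilated patients, it will look slower to walk and no analysis described in the article corrects for that. And in a proportional hazards setting, omitting a prognostic factor pulls the estimated hazard ratio toward 1 and costs power even when the arms are balanced.

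**Working it through.** **1. The plan's own sample size.** Inputs from Statistical analysis: HR 1.87, type 1 error 5% (taken as two-sided), power 0.8, 10% dropout, 88 patients in two arms of 44, all patients in the planning data reaching the endpoint.

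- (1.960 + 0.842)² = 7.849.
- Freedman: (2.87/0.87)² × 7.849 = 85.4, so 86 events.
- Schoenfeld: 4 × 7.849/(ln 1.87)² = 80.1, so 81 events; 81/0.90 = 90 patients.

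Both routes come within 2 of the stated 88. The sample size is not in question here.

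**2. Chance imbalance.** With 44 per arm, the between-arm difference in mean (log) ventilation days has SD √(2/44) = 0.213 in SD units. The probability that it exceeds 0.2 SD in either direction is 35%, and 0.3 SD is 16%.

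The document gives no prognostic strength, so a range is assumed. If each SD multiplies the hazard of reaching FAC 3 by 0.7, then −ln 0.7 = 0.357, and an imbalance of k times 0.213 shifts the hazard ratio by about exp(±0.357 × 0.213 × k):

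- k = 1: 1.87 becomes about 1.73 or 2.02.
- k = 2: 1.87 becomes about 1.61 or 2.18.

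**3. Power, with ventilation as the only covariate.** Simulation: 88 patients, 1:1, exponential times, 10% random censoring (about 79 events), conditional HR 1.87, standard-normal covariate.

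| Hazard factor per SD | Power, unadjusted | Power, adjusted | Gain |
|---|---|---|---|
| 1.0 (no effect) | 78% | 77% | −1 |
| 0.8 | 75% | 78% | 3 |
| 0.7 | 70% | 79% | 9 |
| 0.6 | 64% | 77% | 13 |

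Repeat simulations agree to within about two points per cell. At a factor of 0.6 the unadjusted hazard ratio averages about 1.7, against about 1.9 adjusted. With no treatment effect the rejection rate is about 5% in either analysis.

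**4. Power, with MRC sum-score already in the model.** Assumptions: MRC hazard factor 0.7 per SD, correlation 0.5 with ventilation duration.

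| Residual ventilation factor per SD | MRC only | MRC plus ventilation | Gain |
|---|---|---|---|
| 0.85 or 0.8 | 77% | 78% | 1 |
| 0.7 | 73% | 78% | 5 |

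Where the MRC score is fitted, it takes up much of what ventilation duration would otherwise add.

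**The case against.** **No validity error.** Randomisation balances ventilation duration in expectation, and chance imbalance in an unlisted variable is ordinary sampling variation, already reflected in the confidence interval. This stands. A reader might infer that the trial's result would be biased or its type I error inflated; neither follows.

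**The large power figures use a harsh baseline.** They compare ventilation alone with no covariate at all. MRC and FAC measure the weakness through which long ventilation plausibly acts, and with MRC in the model the gain is about 1 to 5 points. This stands, with one limit: under the present rule MRC enters only if its own imbalance threshold is met.

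**1.87 may already be a marginal hazard ratio.** The article reports it from the data of 35 patients and mentions no adjustment. If it is unadjusted, the attenuation is already in it, and unadjusted power stays near 79 to 81%. This also stands: the figures show what adjustment can gain, and a reader should not take them as proof that the trial falls short of its planned 80%.

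**The prognostic claim is qualitative.** Eligibility criteria supports a population threshold. It does not show that days beyond 48 hours strongly predict recovery among patients who already meet the functional entry criteria. Fair, and the reason for giving a range that includes no effect.

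**Adding a name to the list would not deliver the gain.** Under the imbalance trigger, a fifth covariate would correct only an observed imbalance. That is correct and shapes the fix.

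**An unseen analysis plan may add the covariate.** Possible. But the article does more than leave the choice open: it names specific covariates with numeric thresholds and a stated reason, and by that reason ventilation duration belongs with them.

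**Conclusion.** The point holds as an inconsistency between the eligibility rationale and the covariates named for the primary outcome. Its consequence is uncorrected chance imbalance and some lost precision.

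The gain from adjustment is about 3 to 13 power points against an unadjusted analysis (hazard factor 0.8 to 0.6 per SD, conditional HR 1.87). It is about 1 to 5 points if a correlated MRC sum-score is already fitted (residual factor 0.85 to 0.7). These strengths, and the correlation of 0.5, are assumptions; the document gives only the direction.

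Two stronger readings are not supported. The document does not show ventilation duration to be a strong predictor within the enrolled population. Nor does it show that the needed value is already collected: the listed endpoint is a duration that can include time after randomisation, and the characteristics after Fig. 2 do not name the earlier part. The change is worth making because it is cheap and follows from the protocol's own reasoning; the trial remains valid without it.

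**What to change.** In Statistical analysis, prespecify log days of mechanical ventilation, from the start of ventilation to randomisation, as a covariate of the Cox model for time to FAC 3, and fit that model whether or not a baseline imbalance is observed. Do not use the total duration listed under Secondary endpoints, because treatment may affect the part after randomisation.

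Add the variable to the recorded baseline characteristics. The start of ventilation must already be known to check the 48-hour criterion, so it needs no new measurement.

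The cost is one sentence in the analysis section, one baseline field, and one more model term with about 80 events. If ventilation duration turns out not to be prognostic, the loss is at most about one power point. The sample size of 88 does not change.

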#### Inclusion criteria

Participants have to be mechanical ventilated for ≥ 48 hours, must be responsive and able to follow instructions according to the Short 5-item Questionnaire (S5Q 5 out of 5) [18], have quadriceps muscle strength ≥ 2 according to the Medical Research Council [19] and must be able to sit unsupported on the edge of the bed.

#### Exclusion criteria

Exclusion criteria are; the presence of contraindications for physiotherapy according to the evidence statement for ICU physiotherapy [18] such as heart rate of < 40 or > 130 beats per minute, a recent myocardial ischemia or a mean arterial pressure (MAP) of < 60 or > 110 mmHg, surgical contraindications (i.e. instable fractures, craniotomy, open abdomen or thorax), insufficient knowledge of the Dutch language, inability to walk independently in the month prior to ICU admission, one or more amputated lower extremities, mental retardation and when death is imminent. Patients with neurological diseases and disorders as indication for ICU admission are excluded because underlying pathology may affect recovery of functional walking ability.

#### Recruitment

All patients admitted to the ICU for > 48 hours will be screened daily for eligibility.

Patients who fulfil the inclusion criteria will be invited to participate in the study. In case of severe muscle weakness and inability to provide written informed consent, verbal consent will be obtained, and an independent witness will sign on behalf of the participant. Participants can leave the study at any time for any reason if they wish to do so without any consequences.

### Randomization and blinding

We will use a variable block randomization method performed by the software CASTOR EDC, a Good Clinical Practice (GCP)-approved online software service. These variable blocks are of various sizes. This way the researcher does not know how large the blocks are at any given moment, and thus cannot predict the next randomization. After randomization, the patient identification number (PIN) number and treatment allocation will be provided to the physiotherapist performing the interventions. Due to the kind of the intervention, it is not possible to blind physiotherapists and participants for the intervention. The primary outcome will be assessed by a researcher who is blinded for the intervention. Secondary outcomes will be assessed by blinded researchers except during the stay of the participants in the ICU where measurements will be assessed by the physiotherapist during treatment (usual care and intervention) to avoid too much strain on the patients.

### Treatment of subjects

#### Treatment before enrollment

Patients will be screened for eligibility at a daily basis. Patients who do not meet the criteria to enter the study but are considered potentially eligible for inclusion at a later time, will receive physiotherapy according to usual care but no BWSTT. Potentially eligible patients are those patients who are unable to perform ambulation exercises out of bed at the time of screening but are likely to improve over time. They may be sedated, hemodynamically instable, have delirium and/or too severe muscle weakness to be mobilized. For these patients, usual care physiotherapy consists of passive and (guided) active exercises in bed, passive and partially active cycling in bed if possible, inspiratory muscle training (IMT), transfer training to the bedside and active balance training in a seated position [7, 18, 20]. Training load in terms of frequency, intensity, type and time will be adjusted according to the physical capacity of the patient.

#### BWSTT intervention

Participants in the intervention group will receive BWSTT in addition to usual care. The BWSST intervention consists of walking on a treadmill while supported by a harness (see Fig. 1 for a schematic illustration of the BWST).

**Fig. 1 Fig1:**
[figure not shown]
Schematic illustration of the BWST

A mobile treadmill with weight-bearing utility will be used for BWSTT (Fig. 1). The body weight-supported treadmill enables early ambulation in patients with insufficient motor control or muscle strength to fully bear weight. The treadmill has been developed in the Amsterdam UMC.

The intervention will be provided by trained physiotherapists. BWSTT is provided on a daily basis for 5 days per week (not during the weekend) in the ICU or medium-ICU (MICU) and the regular ward.

For each session, two physiotherapists are involved. Before the BWSTT, the patient is seated upright at the side of the bed and the harness is fitted. The treadmill is positioned at the bedside and the harness is fastened to the safety lines attached to the frame of the BWST to support bodyweight. One physiotherapist stands next to the BWST to adjust the amount of bodyweight support and to monitor vital functions at the bedside monitor. The second physiotherapist guides the patient and coordinates the intervention in terms of walking speed and distance depending on the walking capacity of the patient. The aim is to have the patient walk at a self-chosen comfortable walking speed. The intervention stops as the vital signs exceed the safety criteria [18], the patient indicates that he has reached his maximum load, or according to the clinical observation of the patient by the physiotherapist. After a period of recovery, if vital signs and perceived exertion return to pre-exercise levels, the physiotherapist may decide to continue BWSTT in consultation with patient and medical staff in order to reach a sufficient training load. This exercise can be repeated multiple times before the intervention is ended. When the intervention is ended the harness is removed while the patient is seated at the bedside, the patient will then be guided back to a supine position in bed.

After ICU discharge, BWSTT will be continued daily on the regular ward until the patient is able to ambulate with walking aid and minimal physical support for balance assistance (Functional Ambulation Categories [FAC] ≥ 2). Physiotherapy according to usual care will be provided from that point on until hospital discharge.

